### 7.1.4 Management of Skin Toxicity

It is strongly recommended that all patients follow a program of sun protective measures while receiving study therapy and for 3-4 weeks after discontinuing study therapy. The aim is to reduce the risk of development of skin rash, minimize the severity of skin rash, and to minimize the requirement for dose reduction of study therapy.

If a patient develops a skin rash, the following actions are recommended to the Investigator for the management of this reaction:

- A variety of agents can be used to manage skin rashes. These include mild to moderate strength steroid creams, topical or systemic antibiotics, topical or systemic antihistamines, and occasionally retinoid creams.
- The rash should be graded/assessed by a physician as soon as possible according to the CTCAE cutaneous toxicity criteria and documented accordingly.
- If a rash of CTCAE grade 2 or higher is detected, immediate symptomatic treatment should be provided.
- If a rash of CTCAE grade 3 is detected, ZD6474 should be withheld until recovery to grade 1 or below. ZD6474 should be dose reduced as per section 7.1.1.

- Grade 4 rash will result in study withdrawal

If ZD6474 must be withheld for >3 weeks due to cutaneous toxicity, the patient will be withdrawn from study.

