## **7 DOSE and SCHEDULE MODIFICATIONS**

This Phase I study is intended to establish the maximum tolerated dose (MTD) of the combination of cetuximab, ZD6474 and irinotecan. DLTs (defined as within the first 28 days of treatment in dose level 1 and first 35 days in dose levels 2-4) will include: grade IV hematological toxicity > 7 days; fever and neutropenia; grade III diarrhea leading to hospitalization or lasting > 48 hours despite aggressive anti-diarrheal medication; grade IV diarrhea despite aggressive anti-diarrheal medication; grade IV vomiting despite optimal antiemetics; or grade III or higher nonhematological toxicity (excluding nausea, vomiting, diarrhea, or alopecia) lasting > 1 week; grade 4 skin toxicity; grade 3 or greater cardiac toxicities; or death. If patients in dose levels 2-4 who have a DLT in the first 14 days (prior to initiation of irinotecan), the patient will not be counted towards the DLTs of that cohort and an additional patient will be substituted. For example, if one of the first 3 patients in dose level 3 have a DLT, that patient will not be calculated into the DLT tabulation for ZD6474, cetuximab and irinotecan and an additional patient will be substituted in that spot. If this scenario occurs twice, the study will be held and the study team will reevaluate the ZD6474 / cetuximab toxicities.

Patients should remain on the assigned doses of therapy throughout the period of assessment of DLTs (first 28 days in dose level 1 and 35 days in dose levels 2-4) unless a DLT is observed or the patient is withdrawn from study for other reasons. The following guidelines for dosing delay and/or dose modifications apply to patients who either experience a DLT during the first 28 days (dose level 1) or 35 days (dose levels 2-4) OR develop treatment-related toxicities after that period of assessment.

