## 7.1 ZD6474 DOSE MODIFICATIONS

For guidance on the management of QTc prolongation, see Figure 1 below. For all other toxicities, the dose of study treatment will be withheld for up to 3 weeks until the toxicity has resolved to CTCAE grade 1 or better, and then study treatment may be restarted. Patients will be withdrawn from the study if toxicity does not resolve to CTCAE grade 1 or better within 3 weeks. Dose reduction/re-challenge for each toxicity criterion will be managed as discussed in the sections that follow.

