### 7.1.2 QTc PROLONGATION

Patients will have ECGs performed to monitor QTc interval (using Bazett's correction) as outlined in the study plan.

Figure 1 Flowchart detailing management of QTc prolongation

Figure 2 Flowchart detailing management of QTc prolongation

[figure not shown]

For this study, QTc prolongation is defined as:

(1) A single QTc value of  $\geq 550$  msec or an increase of  $\geq 100$  msec from baseline

**OR**

(2) Two consecutive ECG measurements, within 48 hours of one another, in which either of the following criteria are met for both QTc values (the second being the mean of 3 consecutive ECGs):

- A QTc interval  $\geq 500$  msec but  $< 550$  msec **OR**
- An increase of  $\geq 60$  msec, but  $< 100$  msec, from baseline QTc to a QTc value  $\geq 480$  msec.

Use baseline QTc as noted in the Required Data Table (Section 10, ‡)

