#### 7.1.6 Management of Other Toxicity

If any other grade 3 or 4 toxicity that is not outlined elsewhere in Sections 7.1 develops and is deemed attributable to ZD6474, ZD6474 should be withheld until the toxicity resolves to grade 1 or below. Upon recovery, treatment may resume at a permanent reduced dose. If ZD6474 must be withheld for more than 3 weeks for resolution of toxicity, the patient will be withdrawn from study.

Patients who develop CTCAE grade 3 hypertension may continue on therapy if blood pressure is controlled on antihypertensive medication. If blood pressure cannot be stabilized with increased antihypertensive medication, study treatment must be discontinued and cannot be resumed until blood pressure is controlled to baseline level. Patients with CTCAE grade 4 hypertension should discontinue study treatment and cannot resume therapy until blood pressure is controlled to baseline level. If study treatment must be interrupted for more than 3 weeks to allow for toxicity to resolve, the patient's study participation will be discontinued.

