| Grade 3 or 4 cutaneous                                               | Withhold dose until toxicity has resolved to CTCAE grade 1 or less, then reduce dose as per section 7.1.4. If ZD6474 must be withheld for $> 3$ weeks due to cutaneous toxicity, the patient will be withdrawn from study.                                                                                                                                                                                                        |
| Other grade 3 or 4 toxicity related to ZD6474                        | Withhold dose until toxicity has resolved to CTCAE grade 1 or less, then reduce dose as per section 7.1.6. If study treatment must be interrupted for more than 3 weeks to allow for toxicity to resolve, the patient's study participation will be discontinued.                                                                                                                                                                 |

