#### 7.2.4 Management of Dermatologic Toxicity

Patients developing dermatologic toxicities while receiving cetuximab should be monitored for the development of inflammatory or infectious sequelae, and appropriate treatment of these symptoms initiated. Since both ZD6474 and cetuximab can lead to dermatological toxicities, the following schema should be followed required dose reductions:

- \* For the first instance of grade 3, dose-reduce ZD6474 only.
- \* For subsequent instances of grade 3 rash, both ZD6474 and cetuximab should be dose reduced

Dose reductions of cetuximab are permanent; no re-escalation of dose is allowed. Cetuximab cannot be held for more than 3 weeks; if cetuximab is held for more than 3 weeks, the patient will need to be discontinued from the trial. Dose reductions of cetuximab are as follows:

| Grade 3 Rash               | Cetuximab                           | Dose modification                   |
|----------------------------|-------------------------------------|-------------------------------------|
| 1 st occurrence | Hold infusion until grade 1 or less | Continue at 250 mg/m  * |
| 2 nd occurrence | Hold until grade 1 or less          | Reduce to 200 mg/m      |
| 3 rd occurrence | Hold until grade 1 or less          | Reduce to 150 mg/m      |
| 4 th occurrence | Discontinue study treatment         |                                     |

\* ZD6474 will be reduced for first occurrence

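### The ZD6474 summary table in 7.1.7 restarts treatment after grade 4 rash, which 7.1.4 makes a withdrawal; two narrower dose rules also conflict

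*Protocol*

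**What the plan says.** **Rash.** Protocol 7.1.4 treats grades 3 and 4 separately. At grade 3, ZD6474 is held until grade 1 or below and reduced under 7.1.1. For the next grade the text is "Grade 4 rash will result in study withdrawal". The summary table in 7.1.7 has one row for both grades, "Grade 3 or 4 cutaneous", with the action "Withhold dose until toxicity has resolved to CTCAE grade 1 or less, then reduce dose as per section 7.1.4". In that row withdrawal follows only if the hold lasts more than 3 weeks. The joint ZD6474/cetuximab rash scheme in 7.2.4 (dermatologic toxicity) starts with "For the first instance of grade 3, dose-reduce ZD6474 only" and addresses grade 3 only.

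**Scope.** Section 7 says "The following guidelines for dosing delay and/or dose modifications apply to patients who either experience a DLT" in the assessment window, and also to patients with treatment-related toxicity after it. Grade 4 skin toxicity is on the DLT list in sections 3.2 and 7.

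**QTc.** The definition in 7.1.2 opens "For this study, QTc prolongation is defined as". It counts a rise of 60 to under 100 msec only if QTc reaches at least 480 msec, and 7.1.3 repeats that floor. The second QTc row of 7.1.7 is triggered by QTc of 500 msec or more, or by a rise of 60 msec or more, with no floor. Section 7.1 also says "For guidance on the management of QTc prolongation, see Figure 1 below"; the figure is not shown in this copy.

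**Irinotecan.** Section 7.3 requires other irinotecan-related toxicity to be grade 1 or less before resumption, and takes the patient off protocol treatment if the delay exceeds 3 weeks. Section 7.3.5 resumes one level lower once an other grade 3/4 toxicity has come down to grade 2.

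**The concern.** A summary table is what a site is likely to have to hand when a toxicity occurs. Here it contradicts the body text on one of the most serious skin events, in a regimen where 7.2.4 recognises that both ZD6474 and cetuximab cause skin toxicity. A site working from the table could give ZD6474 again to a patient whom 7.1.4 withdraws.

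The other two conflicts carry less. The QTc row could cost a patient dose that 7.1.2 and 7.1.3 would not take away. The irinotecan rules leave it open whether a patient whose toxicity has settled at grade 2 resumes treatment or waits and may be removed.

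**Working it through.** No figure in the plan has to be reproduced. The check sets the rules side by side and works through cases.

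**1. Grade 4 rash that resolves to grade 1 within 3 weeks**

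| Source | Outcome |
|---|---|
| 7.1.4 | Withdrawn from study |
| 7.1.7, cutaneous row | ZD6474 restarted at a reduced dose |
| 7.2.4 (dermatologic) | No rule; grade 3 only |

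The dose restarted under 7.1.7, using the 7.1.1 table, is 300 to 200 mg, 200 to 100 mg, or 100 mg daily to 100 mg every other day. The row cites 7.1.4 as the basis for the reduction, but 7.1.4 contains no reduction at grade 4. The silence of 7.2.4 is consistent with 7.1.4 and gives no support to the table.

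**2. QTc rise of 60 to under 100 msec that stays below 480 msec**

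With baseline *b*, the texts disagree for QTc from *b* + 60 up to, but not including, min(480, *b* + 100). The upper limit applies because a rise of 100 msec or more counts under every text. The range is empty once *b* + 60 ≥ 480, that is, *b* ≥ 420.

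| Baseline (msec) | Disputed QTc (msec) | Width (msec) |
|---|---|---|
| 360 | 420 to <460 | 40 |
| 380 | 440 to <480 | 40 |
| 390 | 450 to <480 | 30 |
| 400 | 460 to <480 | 20 |
| 410 | 470 to <480 | 10 |
| 419 | 479 to <480 | 1 |
| 420 or more | none | 0 |

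Example: baseline 400, on-treatment QTc 465, a rise of 465 − 400 = 65 msec, confirmed on repeat. Under 7.1.2 and 7.1.3 this is not prolongation and dosing continues unchanged. Under 7.1.7 the triplicate ECG is repeated. What follows depends on which criteria the repeat must meet:
- If they are those of the 7.1.2 definition, dosing continues, and the only difference is one extra triplicate ECG.
- If they are the row's own trigger, ZD6474 is held and then reduced, and 7.1.1 makes reductions permanent.

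**3. Other irinotecan toxicity that reached grade 3/4 and is now grade 2**

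| Source | Outcome |
|---|---|
| 7.3 | May not resume; off protocol treatment if the delay exceeds 3 weeks |
| 7.3.5 | Resume one level lower (from 180 to 150 mg/m² by the 7.3.1 table) |

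Other toxicity that never exceeds grade 2 is not affected, because 7.3.5 continues irinotecan. Late diarrhea and nausea/emesis are not affected either: both parts numbered 7.3.4 require grade 1 or less, as 7.3 does.

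**The case against.** **Rash.** The table is only a summary. Its row concerns cutaneous toxicity in general, and it sends the reader to 7.1.4, where the grade 4 line directly follows the grade 3 line. On this view 7.1.4 governs, and re-dosing happens only if a site ignores the pointer. It is reasonable to take 7.1.4 as the intended rule, but the conflict remains. Grade 4 rash falls within both texts, the row names grade 4 explicitly and gives it an action, and following the pointer exposes the contradiction without resolving it. The objection that 7.2.4 supports 7.1.4 only by silence is fair; that support is secondary.

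**QTc.** The row's wording about meeting criteria resembles 7.1.3, which refers to the study-wide definition, so the lenient reading is plausible. A QTc of 465 msec is also already below the row's own 480 msec recovery threshold, which makes the strict reading awkward. Both points reduce the weight. They do not remove the gap: read literally, the row still ends in a reduced dose. The figure named in 7.1 might settle the matter but cannot be consulted here.

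**Irinotecan.** A specific rule normally overrides a general one, and the 7.3.5 table is coherent in itself, since it continues irinotecan at grade 2. It may well be a deliberate exception. Section 7.3 does not say so, however, and its requirement is worded to cover every other irinotecan-related toxicity. It is also true that removal follows only if the toxicity stays above grade 1 until the delay exceeds 3 weeks; otherwise the difference is a delay.

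**Conclusion.** The concern holds. The rash conflict is the substantive one: for a grade 4 rash that settles within 3 weeks, the protocol orders both withdrawal and re-dosing one level lower. It should be corrected because it bears on re-exposure after a dose-limiting skin event.

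The QTc gap is confined to baselines below 420 msec, spans at most 40 msec, and adds no safety risk, because the table is the stricter text. Its cost is one extra triplicate ECG or, on the literal reading, a hold and a permanent reduction. The irinotecan gap is confined to other toxicities that fall from grade 3/4 to grade 2.

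All three points concern patient management and later exposure. Grade 4 skin toxicity in the assessment window is a DLT whichever rule is followed, so the DLT definition and the MTD rule are unaffected. The protocol gives no frequencies for these situations, so the number of patients concerned cannot be estimated. The reading of the QTc row rests on the text alone, without the figure.

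**What to change.** 1. **Cutaneous row of 7.1.7.** Limit the hold-and-reduce action for rash to grade 3, and add a line stating that grade 4 rash means withdrawal under 7.1.4. Leave non-rash grade 4 skin events under the existing hold-and-reduce rule unless the clinical team decides otherwise. The action is the same as in 7.1.6, but that section covers "any other grade 3 or 4 toxicity that is not outlined elsewhere in Sections 7.1" and 7.1.4 is headed as skin toxicity, so the team should confirm the choice.
2. **Second QTc row of 7.1.7.** Add that the 60 msec rise must reach a QTc of at least 480 msec. As clerical clean-up, change the pointer to section 3.3.5.1, which does not exist in this protocol, to 7.1.1 in both QTc rows.
3. **Irinotecan.** State one resumption grade for other toxicities: either name 7.3.5 as an explicit exception in 7.3, or change 7.3.5 to grade 1 or less, as the clinical team decides.

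The cost is protocol wording only: one table row, one QTc phrase, one cross-reference that appears in two rows, and one sentence in 7.3 or one grade in 7.3.5. No change to the design, sample size or analysis is needed.

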#### 7.1.5 Management of Gastrointestinal Toxicity

Nausea, vomiting, or both may be controlled with antiemetic therapy. Diarrhea should be treated with standard medications to avoid dose modification or interruption, if possible. Electrolyte supplementation with regular laboratory monitoring should be used, when appropriate, to maintain electrolytes within normal limits and prevent an increased risk of QTc prolongation. No dose modifications will be made because of grade 1 or 2 diarrhea. If grade 3 diarrhea develops, ZD6474 should be withheld until diarrhea resolves to grade 1 or below. Patients who are clinically unstable because of diarrhea or other intercurrent medical illness must be admitted and evaluated using telemetry, until clinically stable. Upon recovery, ZD474 may resume at a permanently reduced dose if patient developed diarrhea in the setting of optimal antidiarrheal management; else ZD6474 can be maintained at the same dose or reduced (at discretion of treating physician) and patient must be instructed as to optimal diarrhea management. If ZD6474 must be withheld for more than 3 weeks for resolution of diarrhea, the patient will withdrawn from study.

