### 7.3 Irinotecan Dose Reductions

Treatment with irinotecan can resume if  $ANC \geq 1200/mm^3$ , the platelet count is  $\geq 100,000/mm^3$ , and any other irinotecan-related toxicity resolved to  $\leq$  grade 1. If irinotecan is held for irinotecan-related toxicities that are not attributable to ZD6474 or cetuximab, treatment with cetuximab and ZD6474 may continue. **Irinotecan cannot be delayed for more than 3 weeks or the patient should be removed from protocol therapy.**

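### For severe diarrhea attributed to irinotecan alone, Sections 7.1.5 and 7.3 give opposing instructions on ZD6474 at grade 3, and grade 4 is left unreconciled

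*Protocol*

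**What the plan says.** The protocol deals with ZD6474 during diarrhea in several places.

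- **Section 7.1, opening.** For toxicities other than QTc prolongation, study treatment is withheld for up to 3 weeks until grade 1 or better. Neither a threshold grade nor a cause is named.
- **Section 7.1.5 (gastrointestinal).** "If grade 3 diarrhea develops, ZD6474 should be withheld until diarrhea resolves to grade 1 or below". There is no attribution condition, and the sentence does not name grade 4. On restart, ZD6474 "may resume at a permanently reduced dose if patient developed diarrhea in the setting of optimal antidiarrheal management". If that management was not optimal, the same dose or a reduced one is allowed at the physician's discretion.
- **Section 7.1.6 (other toxicity).** Its scope is limited at the outset: "If any other grade 3 or 4 toxicity that is not outlined elsewhere in Sections 7.1 develops and is deemed attributable to ZD6474". Within that scope ZD6474 is withheld, and then "Upon recovery, treatment may resume at a permanent reduced dose".
- **Section 7.1.7 (summary table).** There are rows for QTc, cutaneous and other grade 3 or 4 toxicity related to ZD6474, but none for diarrhea. The last row reads "Withhold dose until toxicity has resolved to CTCAE grade 1 or less, then reduce dose as per section 7.1.6".
- **Section 7.3 (irinotecan).** When irinotecan is held for irinotecan-related toxicity not attributable to the other two drugs, "treatment with cetuximab and ZD6474 may continue". Section 7.3.4 (late diarrhea) holds irinotecan for grade 2, 3 or 4 diarrhea and does not mention ZD6474.
- **Alert Page, clarification to Section 4.2.** In explaining the potassium rule for ZD6474, it gives CTCAE grade 3 as the cut-off for holding, as for other toxicities, with no reference to cause.

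**The concern.** Diarrhea is a toxicity that the drugs share. The protocol calls it a major dose-limiting toxicity of irinotecan (Section 6.2). It also reports any-grade diarrhea in 55.4% of patients on ZD6474 300 mg alone and 50.0% on 300 mg with docetaxel (Section 6.1). A patient on the triplet with grade 3 or 4 diarrhea may therefore fall under both the ZD6474 rules and the irinotecan rules. Those rules part company when the investigator attributes the event to irinotecan alone.

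Two things are at stake. The first is safety on the protocol's own reasoning: 7.1.5 ties electrolyte control during gastrointestinal toxicity to QTc risk, so continuing ZD6474 through severe diarrhea is not a neutral matter. The second is the delivered dose of ZD6474, the only drug escalated from level 2 to level 4. Across the three expected centers, it could depend on which section was followed.

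**Working it through.** No sample size, error rate or published figure is involved, so the check sets the sections side by side.

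**Does diarrhea trigger the 7.3 permission?** Yes. Section 7.3.4 (late diarrhea) holds irinotecan for grade 3 and grade 4. If the event is attributed to irinotecan alone, both conditions in 7.3 are met.

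**Whether ZD6474 is withheld**

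| Grade, attribution | 7.1 opening | 7.1.5 | 7.1.6 / 7.1.7 | 7.3 | Result |
|---|---|---|---|---|---|
| 3, ZD6474 | withhold | withhold | 7.1.6 excludes it (covered in 7.1.5); the 7.1.7 row read alone withholds | does not apply | agree |
| 3, irinotecan alone | withhold | withhold | do not apply | may continue | **conflict** |
| 4, ZD6474 | withhold | not named | withhold | does not apply | agree; gap in 7.1.5 only |
| 4, irinotecan alone | withhold | not named | do not apply | may continue | **unreconciled** |

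The Alert Page cut-off points to holding in all four rows, although it was written about potassium. In the last row, a reader who follows 7.3 treats grade 4 diarrhea less strictly for ZD6474 than 7.1.5 treats grade 3.

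**Is there a rule of precedence?** None is stated. Section 7.1.5 is specific to the event, and 7.3 is specific to the attribution. The missing attribution condition in 7.1.5 cannot be assumed to be shorthand, since 7.1.6, the next section, does state one. For rash, which ZD6474 and cetuximab share, Section 7.2.4 sets a joint scheme. Diarrhea has no counterpart.

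**Restart dose, grade 3, related to ZD6474**

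| Antidiarrheal management | 7.1.5 | 7.1.7 row read alone | Result |
|---|---|---|---|
| Optimal | reduced | reduced | agree |
| Not optimal | same or reduced | reduced | mismatch in the table |

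Section 7.3 sets no ZD6474 restart dose.

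**Size for one affected patient.** Under 7.3, ZD6474 may stay at the assigned dose. Under 7.1.5 it is paused and, after optimal antidiarrheal management, may resume one step down. Section 7.1.1 makes that step permanent:

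- 300 to 200 mg: 100/300 = 33% lower
- 200 to 100 mg: 100/200 = 50% lower
- 100 mg daily to 100 mg every other day (mean 50 mg per day): 50/100 = 50% lower

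**When the rules operate.** The opening of Section 7 keeps patients on assigned doses during the DLT window (28 days at level 1, 35 days at levels 2 to 4) unless a DLT occurs or the patient is withdrawn. The modification rules apply after a DLT in the window, or to treatment-related toxicity after it.

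**The case against.** The best reply is that 7.3 is permissive. It may mean only that holding irinotecan does not in itself oblige anyone to hold the other two drugs, leaving 7.1.5 to govern ZD6474. That reading is coherent, but the protocol does not state it, and the plain words of 7.3 support the other reading equally well.

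Three further objections limit the point:

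- The 7.3 condition is met only when neither ZD6474 nor cetuximab is implicated. With a shared toxicity that may be uncommon. This limits how often the conflict arises, but does not remove it.
- Grade 4 is not without a rule, because the opening of 7.1 and the Alert Page both point to holding. That stands. The difficulty is that 7.3 permits the opposite.
- The 7.1.7 row cites 7.1.6 and can be taken to share its limited scope. That also stands: the restart-dose mismatch arises only for someone using the table without the sections behind it.

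Three stronger readings are tempting, and the documents do not support them:

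- *The conflict covers all grade 3 or 4 diarrhea.* When the event is attributed to ZD6474, the applicable sections agree on withholding. Nor does 7.1.6 contradict 7.1.5 at grade 3, because it excludes toxicities covered elsewhere in 7.1.
- *The conflict shifts the DLT count and hence escalation.* Section 3.2 defines diarrhea DLTs by grade, duration, hospitalization and response to antidiarrheal medication, not by whether ZD6474 was held. Within the window, the hold rules start only once a DLT has occurred.
- *A share of the 34 patients can be named as affected.* The protocol gives no grade 3 or 4 diarrhea rate for the triplet. Level 1 patients receive no irinotecan, and only events attributed to irinotecan alone are contested.

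**Conclusion.** The point holds in a limited form. For diarrhea attributed to irinotecan alone, in patients given irinotecan, 7.1.5 and 7.3 oppose each other at grade 3. At grade 4, 7.3 opposes the general hold rules while the hold sentence of 7.1.5 is silent. The 7.1.7 table is a secondary, editorial mismatch.

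The number of patients affected cannot be derived from the protocol. The effect on one patient runs from no change in ZD6474 to a pause followed by a possible permanent reduction of 33% to 50%. The upper end assumes that the event occurred under optimal antidiarrheal management and that the patient restarts one step down.

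The MTD decision is not put in doubt by this inconsistency. It deserves correction because it leaves contradictory hold orders on a toxicity that the protocol itself links to QTc risk. Accrual closed in May 2010, but treatment runs to progression (Section 3.5), so the wording still governs anyone on therapy.

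**What to change.** Reconcile the Alert Page clarification, the opening of 7.1, Sections 7.1.5, 7.1.6, 7.1.7 and 7.3, and the late-diarrhea part of 7.3.4, so that grade 3 and grade 4 diarrhea each carry one ZD6474 instruction. It should settle:

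1. whether ZD6474 is withheld;
2. whether attribution to a particular drug matters;
3. how the restart dose is set, including when antidiarrheal management was not optimal.

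State in 7.3 how its permission relates to 7.1.5, and make the 7.1.7 table match, for instance with a diarrhea row. Which clinical rule applies is for the investigators, and none is proposed here. The cost is amendment wording, with no added patients, visits or tests.
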